#### Follow-up

The study outcome measurement and follow-up schedule is detailed in Table 2. Several ideas to limit the missing data were followed in designing the ESCAPE trial [30]. This trial will be undertaken following the routine schedule of the NCD clinics to which diabetes and hypertension patients make regular visits for medical checkups and receiving drugs. Since the study population is routinely served by the PCUs, the chance of dropout is limited. Participants are regular and long-term clients of PCU health services. The rapport between NCD patients and PCU nurses may strengthen the follow-up and minimize the dropout in the trial.

**Table 2 T2:** Overview of data collection and measurements in all three arms of ESCAPE study

	**Follow-up**												
Visit number	1	2	3	4	5	6	7	8	9	10	11	12	13
Month	0	1	2	3	4	5	6	7	8	9	10	11	12
Inclusion and exclusion criteria	x												
Framingham scoring	x						x						x
Self-reported smoking cessation	x			x			x						x
Smokerlyzer	x						x						x
Fagerstrom Test	x						x						x
Blood pressure	x	x	x	x			x			x			x
BMI	x			x			x						x
Blood glucose	x						x						x
Waist circumference	x						x						x
Hip circumference	x						x						x
HbA1C	x												
Lipid profile	x												
CVD event	x						x						x
CVD death	x						x						x
Questionnaires													
Demography	x												
Questionnaire assessing motivation to stop smoking (MTSS)	x						x						x
Questionnaire assessing cost effectiveness	x						x						x
Questionnaire assessing family support on smoking cessation	x						x						x
Questionnaire assessing health literacy	x						x						x

Moreover, the intervention design is an add-on design in which additional evidence-based components are added to the existing routine service [30]. Regarding the outcome measurement, most of the secondary outcomes are feasible to measure via the routine data collection of the study site hospital network. Furthermore, the sample size has been increased by 20% to compensate for dropouts.

The study is carefully designed randomized controlled trial, evaluating two approaches of active intervention and comparing the rate of behavior change. However, the CVD outcome event rate of the active intervention arms will also be analyzed and compared with that of the non-randomized arm made up of smokers refusing to try to give up smoking. It will require the adjustment of minimal residual confounders. Moreover, there will be different models of covariates used to analyze different outcomes. For instance, adjustments in the comparison of CVD events and deaths between the intervention and control arms may include family history, lifestyle, physical activity, alcohol consumption, dietary habits, current medications and socioeconomic status [25]. To assess physical activity as a covariate, a rapid physical activity assessment scale will be applied [31]. Therefore, possible confounders are collected and will be adjusted appropriately in later analysis [32] (Table 3).

**Table 3 T3:** Confounder measurements

**Confounder**	**Variables**	**How to measure**
Demographic characteristics	Age, sex, social status, family size, educational attainment, occupational history, income	Questionnaire
Lifestyle	Alcohol consumption, physical activity	Questionnaire
Genetic factor	Family history of diabetes, hypertension and CVD	Questionnaire
Drugs	Different medications for diabetes and hypertension	Clinical record
Health literacy [29]	A scale of five questions	Questionnaire of Ishikawa’s scale [29]
Family support	A scale of 16 questions	Questionnaire
Physical activity	RAPA scale [30]	Questionnaire

The level of perceived family support and its impact will vary among participants. Participants in the routine service arm and the refusing to give up arm are not supposed to receive care by a family member, purposefully and systemically trained and empowered by the nurse. However, a participant in the control arm may, by chance, also receive strong family support. In view of this major difference, the impact of family support would be measured and adjusted statistically via multivariable analysis.

### Analyses plan

All analyses for pre-specified outcomes in the trial protocol will strictly follow the intention-to-treat principle [33]. Statistical significance in all statistical analysis will be taken as a *P* value less than 0.05 with a 95% confidence interval. Relative risk (RR) for achieving primary outcome, smokerlyzer-confirmed smoking cessation, will be reported with the 95% confidence interval. Moreover, the number needed to treat (NNT) for achieving smokerlyzer-confirmed smoking cessation by the two intervention arms will be reported [34]. To overcome the contamination of the intervention, complier average causal effect (CACE) analysis will necessarily be applied.

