### Study outcome and outcome measurements

#### Primary outcome

The primary outcome of the study is the smoking cessation rate at the 1-year follow-up, proven by measurement of carbon monoxide in parts per million (ppmCO).

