#### Secondary outcomes

Secondary outcomes of the trial are:

1. Smoking cessation rate at the 6-month follow-up, proven by measurement of (ppmCO).

2. CVD risk measured by the Framingham general cardiovascular risk score at the 12-month follow-up.

3. Blood pressure and heart rate measured at the 6- and 12-month follow-up.

4. Number of CVD events and deaths at the 12-month follow-up.

5. Cost-effectiveness of the health service packages at the 12-month follow-up.

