### Sample size

A total of 328 participants will be randomized to have 164 in the new service arm and 164 in the routine service arm. The sample size for the randomized controlled trial was calculated to have a power of 80% and 95% confidence interval so as to show the difference in primary and secondary outcomes, and the CVD incidence between the new package arm and the routine service arm. It was calculated using the power sample size calculation of Stata version 11, based on the previous year’s smoking cessation rate at the MH (9%), and the estimated cessation rate of the evidence-based package (24%). Additionally, the calculated sample size was increased by 20% to compensate for loss to follow-up.

The sample size for the additional non-randomized arm was calculated at a ratio of 1:3 compared to the total size of the two intervention arms. The power of 90% and 95 percent confidence interval will suffice to see the difference in CVD events between ex-smokers and continuous smokers, assumed as 0.1 and 0.25. Totally the sample size is 440 participants.

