#### Smoking cessation rate

The Smokerlyzer-confirmed smoking cessation rate will be compared between two arms of the RCT, at 6 months and 12 months of follow-up, by applying the chi-square test. The smoking cessation rate will also be compared among the three arms of the study. The factors influencing successful smoking cessation at 12 months will be analyzed by multivariable regression model-adjusting covariates. Continuous variables, such as expired CO levels, the Fagerstrom score and nicotine dependence levels, will be compared using MANOVA.

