Next, the need for support and care may differ among smokers (Figure 4); some patients may need motivation, some may need relief from craving symptoms by nicotine replacement therapy, and some may need buddy support [38]. Close monitoring and the kind support provided by a family member help smokers to succeed in giving up smoking [38,43]. Moreover, public health intervention aiming at lifestyle changes needs to focus on individual as well as social and environmental influences. In consideration of this, a component will be added to the new service package, that of close monitoring and continual support of the smoker by a family member (or other assigned member) using a sticker record diary. Social support may empower the smoker in his/her attempts to give up, while relieving the stigma of smoking that may be experienced by other family members [43].

Existing evidence suggests that a smoking cessation service, delivered in combination with other health services, might be a more effective approach than the conventional delivery through tobacco clinics [44,45]. The ESCAPE study is strategically designed to improve access to a smoking cessation service within the community. In this study, NCD clinics, regularly attended by patients at risk of CVD, are chosen as the centers to provide the smoking cessation service. Thus, smokers attempting to stop smoking will have easy access to the health service within their community. Moreover, this approach is expected to strengthen the follow-up and minimize the dropout number of participants during the research.

In this study a smoking cessation intervention at the primary health care level in the setting of northern Thailand will be tested. The 5 A approach is currently adopted by many hospitals in Thailand to treat smokers. The existing systems used at the study sites and the human resources available were observed. Based on existing global evidence, a new smoking cessation intervention package has been designed to treat smokers at the primary health care level. Its efficacy will be assessed by outcomes of behavioral change and cardiovascular risk reduction, and the cost effectiveness of achieving those outcomes. It is expected to generate a culturally tailored, practically effective smoking cessation service replicable in other developing countries.

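### The sample size section claims 80% power for secondary outcomes and between-arm CVD incidence, but its own figures give about 8% for CVD incidence, so secondary results get a confirmatory reading the design does not support

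*Protocol article*

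**What the plan says.** The protocol article names one primary outcome: "The primary outcome of the study is the smoking cessation rate at the 1-year follow-up, proven by measurement of carbon monoxide". Five further items are listed under Secondary outcomes: cessation at 6 months, the Framingham score, blood pressure and heart rate, CVD events and deaths, and cost-effectiveness.

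The Sample size section gives 164 per randomised arm (328 in total) at 80% power, "so as to show the difference in primary and secondary outcomes, and the CVD incidence between the new package arm and the routine service arm". Its inputs for those arms are a 9% cessation rate at the hospital in the previous year, an expected 24% with the new package, and a 20% increase for losses. A second paragraph, on the non-randomised arm, assumes CVD event proportions of 0.1 and 0.25 for ex-smokers and continuous smokers.

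The Analyses plan states: "Statistical significance in all statistical analysis will be taken as a *P* value less than 0.05 with a 95% confidence interval". The closing part of the Discussion says of the package: "Its efficacy will be assessed by outcomes of behavioral change and cardiovascular risk reduction, and the cost effectiveness of achieving those outcomes".

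Two places differ on the Framingham score. Study objectives (secondary objective 2) compares it between the intervention and control groups. The Analyses plan, under CVD risk, CVD events and CVD death, compares it, with blood pressure and heart rate, between people who quit and people who went on smoking.

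**The concern.** A sizing statement tells readers which comparisons the trial can answer. This one covers every secondary outcome and CVD incidence, yet the section gives no expected difference or variability for the Framingham score, blood pressure or heart rate. For CVD incidence, figures elsewhere in the same section can be used to test the claim, and they contradict it.

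The harm runs both ways. A non-significant CVD comparison could be read as evidence of no effect from an adequately powered test, when such a result is expected almost regardless of the truth. An isolated P<0.05 on a secondary outcome could be presented as efficacy, because the plan applies one threshold to everything, says the trial was sized for these outcomes, and names cardiovascular risk reduction as part of the efficacy judgement.

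**Working it through.** **The stated sample size.** For 9% versus 24%, two-sided 0.05 and 80% power, the pooled-variance formula is n = [1.96·√(2·p̄(1−p̄)) + 0.8416·√(p₁(1−p₁) + p₀(1−p₀))]² / (p₁−p₀)², with p̄ = 0.165. It gives 95 per arm, or 108 with continuity correction. After a 20% allowance this becomes 114 to 119, or 130 to 135. The stated 164 is not reproduced; it has about 96% power for 9% versus 24%. That mismatch is a separate matter. It matters here only because the primary contrast is more than covered, and no calculation for any other outcome is shown.

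**Expected CVD incidence by arm.** Inputs, all from Sample size: quit rates 24% and 9%; CVD proportions 0.10 (ex-smokers) and 0.25 (continuous smokers). Assumption: the package affects CVD only through quitting.

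- New package: 0.24 × 0.10 + 0.76 × 0.25 = 0.024 + 0.190 = 0.214
- Routine service: 0.09 × 0.10 + 0.91 × 0.25 = 0.009 + 0.2275 = 0.2365
- Difference: 0.0225

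**Power with 164 per arm.**

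- Standard error: √[(0.214 × 0.786 + 0.2365 × 0.7635)/164] = √(0.3488/164) = 0.0461
- Standardised difference: 0.0225/0.0461 = 0.488
- Power: Φ(0.488 − 1.96) + Φ(−0.488 − 1.96) = 0.0705 + 0.0072, about 7.8%

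With 20% lost (164 × 0.8 ≈ 131 per arm) it is about 7.2%. For 80% power the same variance would need (1.96 + 0.8416)² × 0.3488/0.0225², about 5,400 per arm.

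**False positives among the secondary outcomes.** The Analyses plan writes three secondary tests between the randomised arms: 6-month cessation, CVD events and CVD deaths. The Framingham comparison in Study objectives makes a fourth. The table gives the chance of at least one two-sided P<0.05 when none of these outcomes is affected. The independent case is 1 − 0.95^k; the others assume equally correlated normal test statistics. The documents give no correlation, so a range is shown.

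| Tests | Independent | Correlation 0.5 | Correlation 0.8 |
|---|---|---|---|
| 3 | 14.3% | 12.5% | 9.8% |
| 4 | 18.5% | 15.6% | 11.4% |

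These figures count results in either direction. With three tests at correlation 0.5, a false result favouring the package occurs in about 6.3% of trials. CVD deaths may be too few to contribute much.

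**The case against.** Several objections are fair.

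- **Order among secondary outcomes.** A testing order or alpha split is commonly left to the statistical analysis plan, which is not shown. Its absence here is no finding. One primary outcome and time point is named, and its error rate stays at 5%.
- **Status of the Discussion sentence.** It is closing prose that names outcome domains. It is not a decision rule, and it does not say that one significant secondary result establishes efficacy when the primary is null. That stands; the sentence matters only in combination with the sizing claim and the universal threshold.
- **Power is not type I error.** True. The sizing sentence does not raise the false-positive rate. It is wrong in its own right, and it lends the secondary tests a standing they lack.

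Two stronger readings are tempting but unsupported. A reader might count ten secondary tests (systolic and diastolic pressure and heart rate at two visits, Framingham, 6-month cessation, CVD events, CVD deaths) and infer a 29% chance of a false positive at correlation 0.5. Seven of those ten (Framingham, plus three measures at two visits) are written in the Analyses plan as quitters versus continuous smokers. Those contrasts do not test the package, and their null need not be true when the package does nothing: smoking status is itself part of the Framingham score.

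A reader might also treat "The smoking cessation rate will also be compared among the three arms of the study" as a source of false positives, because it can be significant when the two randomised arms are identical. If people who refused to try quit less often, that null is false and rejecting it is correct. The result simply says nothing about the package.

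**Conclusion.** The point holds as a misstatement in Sample size, with consequences for how the Analyses plan and Discussion will be read. The claimed 80% power for between-arm CVD incidence is about 8% on the protocol's own figures, assuming that those CVD proportions apply over the 1-year follow-up and that the package works only through quitting. For the Framingham score, blood pressure and heart rate, the section offers nothing from which power could be derived. The primary comparison is not threatened. The chance of at least one false positive among the three or four supported arm-versus-arm secondary tests is roughly 10% to 19%, depending on the assumed correlation. That is above 5% but moderate, and it matters because the text invites a confirmatory reading.

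**What to change.** 1. In Sample size, limit the 80% power statement to CO-confirmed cessation at 12 months between the two randomised arms, and remove the reference to secondary outcomes and CVD incidence between those arms.
2. In the Analyses plan, state that the efficacy conclusion rests on that contrast at 0.05, and that secondary and three-arm results are supportive and reported as estimates with 95% confidence intervals. Align the Discussion sentence on efficacy with this. Any formal order among the secondary outcomes can be left to the statistical analysis plan.
3. Reconcile the Framingham comparison in Study objectives (arm versus arm) with the one in the Analyses plan (quitters versus continuous smokers). If both are kept, say that only the arm comparison bears on the package.

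The cost is wording in these sections: no new data, patients or visits, and no loss of power on the primary test. The downside is that an isolated secondary P<0.05 can no longer be presented as evidence of efficacy, and the stated power claim becomes less favourable. The trial was still recruiting when the article was written.

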#### Smoking cessation rate

The Smokerlyzer-confirmed smoking cessation rate will be compared between two arms of the RCT, at 6 months and 12 months of follow-up, by applying the chi-square test. The smoking cessation rate will also be compared among the three arms of the study. The factors influencing successful smoking cessation at 12 months will be analyzed by multivariable regression model-adjusting covariates. Continuous variables, such as expired CO levels, the Fagerstrom score and nicotine dependence levels, will be compared using MANOVA.

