### Study site

Thailand is the study site. Maetha Hospital (MH) is the leading center in this trial. The study will be implemented via the MH network of mobile NCD clinics at seven primary care units (PCU) within the Maetha district. Study site PCUs were chosen based on the eligibility criteria of (1) the presence a regular mobile NCD clinic; (2) a smoking rate among NCD clinic attendants not less than 10%; (3) willingness of the PCU to join the study.

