### Enrollment and randomization

To ensure the required sample size, smoking prevalence among diabetes and hypertension clinics attendants was surveyed. The study site is within the community setting and coupling with non-communicable disease (NCD) clinics, which is expected to promote the smoker’s access to enrollment in the study. Those meeting eligibility criteria will be invited to participate in the study in their routine visit to the PCU. The participants who consent and decide to attempt to stop smoking will be randomly allocated into either the routine service intervention arm or the new service intervention arm. Those who refuse to attempt quitting smoking will be recruited to the non-randomized arm (Figure 1). The randomization site is the NCD clinic at the PCU. Randomization is blocked with the center as a stratum. Random sequences are generated by the statistician on the basis of blocks of 24. The allocated arm for each participant will be provided to the study sites PCUs in opaque, sealed envelopes.

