#### Baseline survey

The balance between an individual’s motivation to stop smoking and his or her degree of dependence on cigarettes determines successful smoking cessation [27]. Thus, those variables will be measured at the outset of the study and at the end of the intervention. Participants will be asked to provide information about their current and past smoking status, such as the number and type of cigarettes smoked, the time they have an urge to smoke in the morning, the source of their cigarettes and details of previous attempts to give up. Breath analysis by smokerlyzer, the Fagerstrom Test for Nicotine Dependence (FTND) and the Nicodep® Test will be applied in order to assess the participant’s smoking status and nicotine dependence [20]. The smoker’s motivation will be measured by the Motivation to Stop Scale (MTSS), a single-item measure composed of key motivational constructs validated by a previous population-based study [28].

Moreover, this trial is assembled to reveal the impact of smoking cessation on the CVD risk among those most at risk. Thus, the FMH score will be measured at the outset of the study and at the end of the follow-up [23,24]. Blood pressure, heart rate, blood glucose, lipid profile, BMI, and waist and hip circumference will be measured, and these data inputs will be used to provide the FMH score [24]. The patient’s current medication for diabetes or hypertension will be recorded, as well as their food preference (salty food, fatty food) and their family history of smoking, including any known CVD events or deaths.

The new evidence-based service intervention will focus not only on the individual, but also on the social environment of the individual, such as their family support. Thus, perceived family support will be measured at the outset. Demographic and socioeconomic information of the participants will also be collected, as well as information regarding costs relating to travel, the provider, client and health service. As a covariate, individual health literacy will briefly be assessed. Measurement of this latent variable will apply communicative and critical health literacy assessment, developed and validated by Ishikawa et al. [29].

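### The arm comparison of cessation is an unstratified, unadjusted chi-square test although randomization is stratified by centre and strong baseline predictors are collected: valid, but it gives up a little precision at no saving

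*Protocol article*

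**What the plan says.** **Design.** Under Enrollment and randomization: "Randomization is blocked with the center as a stratum", and "Random sequences are generated by the statistician on the basis of blocks of 24". Study site describes a network of "mobile NCD clinics at seven primary care units (PCU) within the Maetha district", so there are seven strata.

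**Predictors.** Under Baseline survey, the balance between a smoker's motivation and dependence "determines successful smoking cessation [27]. Thus, those variables will be measured at the outset of the study". That section lists Smokerlyzer breath analysis, the Fagerstrom test, the Nicodep test and the Motivation to Stop Scale (MTSS). Table 2 places Smokerlyzer, Fagerstrom and MTSS at visit 1.

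**Analysis.** Under Smoking cessation rate, the confirmed cessation rate "will be compared between two arms of the RCT, at 6 months and 12 months of follow-up, by applying the chi-square test". Under Analyses plan, the relative risk for "smokerlyzer-confirmed smoking cessation, will be reported with the 95% confidence interval", together with a number needed to treat. Neither place mentions centre or a covariate. For the other smoking measures: "Continuous variables, such as expired CO levels, the Fagerstrom score and nicotine dependence levels, will be compared using MANOVA".

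**Where covariates do appear.** The protocol has a multivariable regression for factors influencing cessation at 12 months, a statistical adjustment for family support, covariate-adjusted cardiovascular comparisons, and a structural equation model that includes motivation. Table 3 (confounders) lists neither centre nor baseline CO, dependence or motivation.

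**The concern.** The analysis does not follow the design. Stratifying by centre removes between-centre variation from the true sampling error of the arm difference. A test that ignores the strata leaves that variation in its estimated error, so if quit rates differ between PCUs the confidence interval is somewhat wider than it need be. In addition, the protocol calls two variables decisive and measures them at the outset, but does not use them in the comparison of the arms. Any chance imbalance in them therefore stays in the headline estimate.

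For the continuous smoking measures, the text promises a comparison by MANOVA without saying whether baseline values enter, and without promising a between-arm difference and interval for each measure.

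At stake are precision and readability of the results, not the validity of the primary conclusion.

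**Working it through.** **1. The plan's own figure.** Inputs from Sample size: 9% versus 24%, 80% power, 95% confidence (taken as two-sided 5%), 164 per arm.

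n per arm = [z(0.975)·√(2·p̄·q̄) + z(0.80)·√(p1q1 + p2q2)]² / d², with p̄ = 0.165 and d = 0.15
= [1.960·√0.27555 + 0.842·√0.2643]² / 0.0225
= (1.0289 + 0.4327)² / 0.0225 = 94.9, so 95 per arm (108 with continuity correction).

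Allowing 20% for loss gives 114 (×1.2) to 119 (÷0.8), or 130 to 135 with the correction. The stated 164 is not reproduced. That is a separate matter, but it bears on the size of this point, because 164 per arm has power Φ[(0.15·√164 − 1.0289)/0.5141] = Φ(1.735) = 95.9% for the planned effect. Little power is left to gain there.

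**2. Cost of ignoring centre and baseline predictors.** I simulated 328 patients in seven near-equal centres, blocks of 24 within centre, two-sided 5%, everyone analysed. There were 5,000 replicates under the null and 2,000 under each alternative. Three analyses were compared on the same data sets:
- the plain chi-square test;
- a Cochran-Mantel-Haenszel (CMH) test by centre;
- a risk-difference regression with centre and one baseline covariate, robust standard errors.

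The protocol gives no centre sizes, centre variation or covariate strength, so those inputs are assumptions, as is the 20% rate in the last column. On the logit scale, a centre SD of 0.5 around 9% puts centres one SD below and above at about 5.7% and 14.0%; an SD of 1.0 puts them at about 3.5% and 21.2%.

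Entries are chi-square / CMH / centre plus covariate, in %.

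| Centre SD, covariate SD | Type I error | Power, 9% v 24% | Power, 9% v 20% |
|---|---|---|---|
| 0, 0 | 5.2 / 5.1 / 5.2 | 95.8 / 95.7 / 95.7 | 81.4 / 81.3 / 81.4 |
| 0.5, 0 | 5.1 / 5.4 / 5.4 | 96.0 / 96.0 / 96.3 | 81.8 / 82.8 / 82.8 |
| 1.0, 0 | 3.7 / 4.9 / 5.1 | 95.9 / 96.4 / 96.5 | 82.8 / 85.1 / 85.2 |
| 0, 0.7 | 5.0 / 4.9 / 5.1 | 95.4 / 95.5 / 96.4 | 81.4 / 81.3 / 83.5 |
| 0.5, 0.7 | 4.7 / 4.9 / 5.1 | 96.5 / 96.6 / 96.9 | 81.7 / 82.2 / 84.2 |
| 1.0, 1.0 | 4.6 / 5.3 / 5.3 | 96.2 / 96.6 / 97.5 | 83.3 / 84.7 / 86.8 |

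The Monte Carlo standard error is √(0.05·0.95/5000) = 0.3 points for type I error and √(0.82·0.18/2000) = 0.9 points for a power near 82%.

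- *Type I error.* The chi-square test never exceeds 5% beyond simulation noise. Only the 3.7% at centre SD 1.0 is clearly below it.
- *Power.* From chi-square to full adjustment, the gain is 0 to 1.3 points at 9% v 24% and 0 to 3.5 points at 9% v 20% (86.8 − 83.3).
- *Source of the gain.* Where both effects are present, the covariate gives more than centre. At SDs of 0.5 and 0.7 (9% v 20%), centre adds 0.5 and the covariate a further 2.0 points; at 1.0 and 1.0, about 1.4 and 2.1. Centre alone adds about 1 point or less unless centres differ strongly (2.3 points at SD 1.0).

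**3. Continuous measures.** Compared with analysing follow-up values alone, adjusting for the baseline value multiplies the variance by 1 − r². With r assumed to be 0.5 to 0.7, that is 0.75 to 0.51, a reduction of 25% to 49%. The protocol gives no r.

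**The case against.** The strongest reply is that an unadjusted primary test with supportive adjusted models is an accepted choice, and that at the planned effect nothing would change: power is about 96% either way. That stands, and it sets the size of the point. Three further arguments have part of the answer.

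- *Adjusted models are already planned.* They are, but they study determinants of quitting or adjust for family support, which the package itself sets out to provide. None is named as the comparison of the arms.
- *An unseen analysis plan may add stratification.* Covariate lists are commonly left to such a plan. But this protocol is not silent: it names the test, and a stratified primary analysis elsewhere would have to supersede it.
- *Baseline motivation may predict less than assumed.* Only people who have agreed to try to quit are randomized, which may narrow the range of MTSS. This is fair, and one reason to read the upper power gains as upper figures.

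A reader might infer more than the text allows:

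- *That the chi-square test is invalid or biased after stratified randomization.* It is not; its error is at worst on the cautious side.
- *That the MANOVA uses follow-up values only, yields a single omnibus P value and drops anyone with a missing component.* The protocol says none of this. Smokerlyzer and Fagerstrom are recorded at months 0, 6 and 12, so a repeated-measures form that uses baseline fits the wording equally well. What can be said is that baseline and centre are not named.
- *That each PCU has its own single nurse, so that centre effects must be large.* The protocol says that each patient keeps the same nurse, not how many nurses a PCU has.
- *That the trial's listed continuous outcomes go to MANOVA.* The sentence concerns smoking measures. Framingham score, blood pressure and heart rate are handled elsewhere with covariates, though by quit status.

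**Conclusion.** The point holds as a modest efficiency improvement. The named arm comparison ignores the randomization stratum and the baseline variables that the protocol itself calls decisive. The cost is about 0 to 1.3 power points at the planned 9% versus 24%, and about 0 to 3.5 if the new package reaches only an assumed 20%. Clear conservatism appears only with strong differences between centres.

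These figures rest on assumed centre and covariate effects, near-equal centres and complete outcomes. They also come from a risk-difference regression with one covariate; the relative-risk model proposed below was not itself simulated. The 25% to 49% variance reduction for the continuous measures applies only if the baseline correlation is 0.5 to 0.7 and the alternative ignores baseline.

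**What to change.** **Cessation.** Make the primary arm comparison one prespecified model for the relative risk: modified Poisson regression with robust standard errors, with arm, PCU, baseline Fagerstrom score and baseline MTSS. Keep the chi-square test as a supportive result, and use the same model at 6 months.

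Keep the covariate list this short. At the planned rates about 164 × 0.09 + 164 × 0.24 = 54 quitters are expected, against nine coefficients beyond the intercept (one for arm, six for PCU, two covariates). State in advance what is done with a PCU that has no quitters, and confirm that both scores are taken before the envelope is opened.

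**Continuous smoking measures.** For CO, Fagerstrom score and dependence, report a between-arm difference with 95% CI for each measure, from an ANCOVA or mixed model with its baseline value and PCU. This can replace the MANOVA or stand beside it.

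**Cost.** Analysis wording only. PCU is known at randomization and the baseline measures are already collected at visit 1. No extra patients, visits or data are needed. The change should be fixed before outcomes are examined by arm.
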